***Anthropometrics***

Anthropometric measurements (weight, height and MUAC) will be analysed using World Health Organization Anthro and Anthroplus version 3.2.2 (WHO, 2011). Weight for age, height-for-age, and weight-for-height will be interpreted using the Z-scores. The Z-scores system expresses the anthropometric values as a number of standard or Z-scores below or above the reference mean or median value (<http://www.who.into/nutgrowthdb/into>, Accessed 15/02/2018). Z-scores, which are gender and age independent thus permitting the evaluation of children’s growth status, will be determined by weight for age (WAZ), height for age (HAZ) and weight for height (WHZ). The Z-scores classification indicated in Table 3.1 was used for interpretation.

**Table 3.1: WHO child growth standard (World Health Organization, 2008)**

| **Z-score** | **Growth indicators** | | | |
| --- | --- | --- | --- | --- |
|  | **Length/height for-age** | **Weight-for age** | **Weight-for length/height** | **BMI-for-age** |
| **Above 3** | See note 1 | See note 2 | Obese | Obese |
| **Above 2** |  |  | Overweight | Overweight |
| **Above 1** |  |  | Possible risk of overweight | Possible risk of overweight |
| **0 (median)** |  |  |  |  |
| **Below -1** |  |  |  |  |
| **Below -2** | Stunted | Underweight | Wasted | Wasted |
| **Below -3** | Severely stunted | Severely underweight | Severely wasted | Severely wasted |

*1. A child in this range is very tall. Tallness is rarely a problem, unless it is so excessive that it may indicate an endocrine disorder such as a growth-hormone-producing tumor. Refer a child in this range for assessment if you suspect an endocrine disorder (e.g. if parents of normal height have a child who is excessively tall for his or her age).*

*2. A child whose weight-for-age falls in this range may have a growth problem, but this is better assessed from weight-for-length/height or BMI-for-age.*

**Interpretation of MUAC indicators**

- MUAC less than 110mm (11.0cm), RED COLOUR, indicates Severe Acute Malnutrition (SAM). The child should be immediately referred for treatment.
- MUAC of between 110mm (11.0cm) and 125mm (12.5cm), RED COLOUR (3-colour Tape) or ORANGE COLOUR (4-colour Tape), indicates Moderate Acute Malnutrition (MAM). The child should be immediately referred for supplementation.
- MUAC of between 125mm (12.5cm) and 135mm (13.5cm), YELLOW COLOUR, indicates that the child is at risk for acute malnutrition and should be counselled and followed-up for Growth Promotion and Monitoring (GPM).
- MUAC over 135mm (13.5cm), GREEN COLOUR, indicates that the child is well nourished.

**
[figure not shown]
Figure 5: MUAC interpretation scale**

According to WHO, the recommended cut-offs for MUAC are valid from 6 months of age and defined as MUAC of less than 115 mm as severe malnutrition and less than 125 mm as malnutrition. Furthermore, MUAC z-scores of −3 SD is defined as severe malnutrition and MUAC z-score of −2 SD as malnutrition. These will be analysed using Anthroplus WHO software.

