***Figure 4: MUAC measuring tape.***

The MUAC is the circumference of the left upper arm that is measured at the mid-point between the tips of the shoulder and elbow. The participant’s left arm will be bent then the researcher will find and mark the mid-point between the two marks. There arm will be hanging straight down, and a MUAC tape will be wrapped around the arm at the midpoint mark. The MUAC will be measured to the nearest 1m (**see Appendix B**) for recording.

1. ***Dietary intake and patterns***

A one day 24-hour recall will be used to collect detailed information about all foods and beverages consumed using the multiple pass method (Steinfeldt *et al*., 2013). Foods will have been consumed in the past 24 hours, most commonly, from midnight to midnight the previous day (**see Appendix C)**. Six daily intervals will be included, namely: breakfast (period up to 09h00), In-between snack (between 09h00 and 12h00), lunch (12h00 to 14h00), In-between snack (14h00 to 18h00), dinner (18h00 to 20h00), and after dinner (after 20h00). Guardian/parents will provide this information. A FFQ will be used to establish food consumption patterns including the *Cucurbita moschata* seeds. A selected pictorial FFQ will be designed for the children to establish if they know and consume the seeds (**see Appendix D**). Preschool menu will also be evaluated at this stage using the 24 hr recall form for recording at least once a week during the implementation of the intervention.

1. ***Biochemical measurements***

Zinc status will be determined by serum zinc concentrations and iron status via haemoglobin, serum ferritin, transferrin receptor and C- reactive protein (CRP) among pre-school children using flame atomic absorption spectrophotometer. The anthropometric status of the preschool children will be assessed by measuring weight and height to calculate the body mass index (BMI).

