**Table 3.5: Proposed data analysis table**

| **Descriptive Statistics** | **Categorical data** | **Numerical data** | |
| --- | --- | --- | --- |
|  |  | **Normally distributed** | **Non-normally distributed** |
| ***Socio demographic information***   - Age - Gender   ***Anthropometric measures***   - Weight, height, MUAC - Categorization according to Z-scores: height for age, weight for age and BMI for age   ***Nutrient intake from 24hr recall***   - Total intake, - Consumption pattern   ***Dietary patterns***  Frequency of inclusion of food item in the FFQ  Morbidity diary  **Biochemical measures**   - Serum zinc - haemoglobin - Serum Ferritin - C-reactive protein - Transferrin saturation - Serum ferritin | Frequencies n (%) | Mean $\pm$ SD | Median and IQR |
| ***Analytical statistics-*** |  |  |  |
| ***Comparison of micronutrient status by subject characteristics*** | Pearson’s Chi-square test/Fishers exact test | ANOVA/T-test | Kruskal-Wallis/Mann-Whitney U tests |
| ***Association between dietary intakes and micronutrient status*** | Regression analyses with dietary intakes and anthropometric indices as dependent variables and all other as independent | | |
| ***Validation of dietary intake and micronutrient status against the intervention*** | Spearman’s correlation coefficient  Comparison of means/means Weighted kappa statistic for agreement testing  Bland Altman plots for bias and agreement testing | | |

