**3.9. Ethical considerations**

No participants will be enrolled into the study until the protocol, participants’ information sheet and recruitment material are approved in writing by the Ethics Committees of the two Universities. The study will be performed in accordance with principles of the Declaration of Helsinki (2013), Good Clinical Practice and the laws of South Africa. No participants will be entered in the study without signed informed consent by parents after the researcher (see Appendix H) has provided a full and adequate oral and written explanation of the study, including possible risks and benefits. Verbal ascent will be obtained from the children before data collection. Consenting process will be conducted in the local languages (*Tshivenda* and *Xitsonga*) and consent forms will be made available in the same languages. Participants will have the right to withdraw from the study at any time. If in the process of the research a participant is diagnosed with a nutrition-related health risk or disease, the parents/guardian will be informed and referred to appropriate health professional or service to address the problem. Data generated from the study will be stored in a computer database, and in a manner, that maintains participants’ confidentiality. For data verification and quality control, purposes regulatory authorities and/ or members of the Ethics Committee of the Universities might be allowed access to participant data under conditions of strict confidentiality. This will be stated in the patient information sheet. The anonymity of participants will be ensured by using codes instead of names and in any publication of the data.

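### The MUAC referral list treats 110–114 mm as moderate malnutrition, although the WHO cut-off cited beside it makes such a child severe

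*Protocol*

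**What the plan says.** All of the relevant text is in the Protocol, section 3.6.2.5, under Interpretation of MUAC indicators, in two parts.

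- **The action list.** Severe: "MUAC less than 110mm (11.0cm), RED COLOUR, indicates Severe Acute Malnutrition (SAM", with immediate referral for treatment. Moderate, 110 to 125 mm: "RED COLOUR (3-colour Tape) or ORANGE COLOUR (4-colour Tape), indicates Moderate Acute Malnutrition (MAM", with the instruction "The child should be immediately referred for supplementation". Two higher bands follow: at risk (125 to 135 mm) and well nourished (over 135 mm).
- **The WHO paragraph**, after Figure 5. It attributes to WHO cut-offs valid from 6 months of age, "defined as MUAC of less than 115 mm as severe malnutrition and less than 125 mm as malnutrition". It then adds MUAC z-scores of −3 SD for severe malnutrition and −2 SD for malnutrition, and closes with a sentence on analysis in the Anthroplus software. It attaches no action to any of these values.

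Four other places bear on the point:

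- The Anthropometrics analysis text says that MUAC will be analysed in the WHO software, but names z-scores only for weight-for-age, height-for-age and weight-for-height.
- Table 3.5 plans "Categorization according to Z-scores: height for age, weight for age and BMI for age", with no MUAC category.
- Section 3.9 says that if a participant is found to have a nutrition-related risk or disease, "the parents/guardian will be informed and referred to appropriate health professional or service to address the problem". It gives no MUAC threshold.
- The record sheet in Appendix B takes MUAC as a number in cm.

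**The concern.** The two absolute cut-offs for severe malnutrition are 5 mm apart, and only the lower one triggers referral for treatment. The protocol presents the higher one as the WHO recommendation and neither adopts it for referral nor explains the departure from it. The children are aged 3 to 5 years, and staff act on the band on the day of measurement. What is at stake is the route of referral: supplementation instead of treatment for a child who is severe by the cited standard. If a severe/moderate split by MUAC were ever reported, its counts would also depend on which cut-off was used.

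**Working it through.** The first check sets the two absolute rules side by side. Both come from Interpretation of MUAC indicators.

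| MUAC reading | Action list | Cited WHO cut-offs | Agree? |
|---|---|---|---|
| below 110 mm | severe, treatment | severe | yes |
| 110 to below 115 mm | moderate, supplementation | severe | **no** |
| 115 to below 125 mm | moderate, supplementation | malnutrition, not severe | yes |

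The conflict is confined to a band of 115 − 110 = 5 mm, that is, whole-millimetre readings 110, 111, 112, 113 and 114. The z-score definition cannot be placed in this table, because the protocol gives no millimetre equivalents for −3 and −2 SD.

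The second check is how many children might fall in the band. The protocol states no MUAC mean or SD, so there is no figure of its own to reproduce. What follows is a range under assumptions.

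- Number of children: n = 436 (Protocol, section 3.4).
- Assumed: MUAC normally distributed, mean μ of 150, 155 or 160 mm, SD σ of 12 or 14 mm.
- Share in the band: p = Φ((115 − μ)/σ) − Φ((110 − μ)/σ).
- Expected children: 436 × p. Chance of at least one: 1 − (1 − p)^436.

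Worked case, μ = 155 and σ = 14: (115 − 155)/14 = −2.857 and (110 − 155)/14 = −3.214. Then p = 0.002137 − 0.000654 = 0.00148, and 436 × 0.00148 = 0.65 children. The chance of at least one is 0.48.

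| Mean (mm) | SD (mm) | Share in band | Expected of 436 | Chance of at least one |
|---|---|---|---|---|
| 150 | 12 | 0.134% | 0.58 | 0.44 |
| 150 | 14 | 0.407% | 1.78 | 0.83 |
| 155 | 12 | 0.034% | 0.15 | 0.14 |
| 155 | 14 | 0.148% | 0.65 | 0.48 |
| 160 | 12 | 0.007% | 0.03 | 0.03 |
| 160 | 14 | 0.048% | 0.21 | 0.19 |

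Five of the six scenarios give fewer than one expected child.

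The third check is what share of the children who are severe by the cited WHO value the action list would call moderate. With μ = 155 and σ = 14, 436 × 0.002137 = 0.93 children are expected below 115 mm. Of these, 0.65 lie in the band, and 0.65/0.93 is about 70%. Over the six scenarios this share runs from 66% to 83%. So the absolute count is small because severe cases are rare, but under these assumptions most of them would fall in the conflicting band.

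**The case against.** The strongest reply is that the two parts serve different purposes. Only the action list tells anyone what to do, so field staff have a single operative referral rule. The WHO paragraph, with its closing sentence on Anthroplus, can be read as the definition for analysis. The Anthropometrics text supports this by naming MUAC among the measurements to be analysed in the WHO software. The first half of the reply stands: a reader might infer that the protocol leaves referral without a governing rule, and it does not. The second half is plausible but not stated. Even if it is granted, the study would refer a child as moderate whom its own analysis calls severe.

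A reader might also infer that there are three competing definitions, counting the z-score. The documents do not support that. The z-score is introduced as a further WHO definition, and with no millimetre equivalent no disagreement with either absolute value can be shown. Nor is the recording precision, "The MUAC will be measured to the nearest 1m", part of the contradiction. It is an evident unit slip.

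The counts are open to challenge as well. They rest wholly on assumed distributions, and the upper end comes from one corner of the grid. The denominator is not fully settled either: the feeding-trial schematic shows 8 preschools × 73 = 584 children, which would raise that corner to 584 × 0.00407 = 2.4. This stands, and it is why the range is offered only as an order of magnitude.

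**Conclusion.** The point holds as an inconsistency in a referral threshold. As written, a child at 110–114 mm goes for supplementation although severe by the WHO cut-off cited in the same section. Nothing elsewhere in the protocol resolves this. The 125 mm limit is common to both schemes.

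The severity is minor. The number affected cannot be computed from the documents. With assumed means of 150–160 mm, SDs of 12–14 mm and a normal distribution, it is about 0 to 2 of 436.

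A reader might infer that malnourished children would be missed. They would not: a child in the band is referred immediately under the action list, and section 3.9 provides a general referral to a health professional. Nor is the trial's result at risk. MUAC is not the zinc or iron outcome, Table 3.5 plans no MUAC category, and MUAC is recorded as a number, so any cut-off can be applied later.

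**What to change.** Rewrite the action list so that referral rests on the measured value in mm and not on the tape colour:

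- severe acute malnutrition, MUAC below 115 mm: refer for treatment;
- moderate acute malnutrition, MUAC 115 to below 125 mm: refer for supplementation.

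The investigators should confirm these thresholds clinically. State that any MUAC category reported will use the same absolute cut-offs.

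The cost is one paragraph of protocol text and a matching change to the field-worker instructions. Sample size and the zinc and iron analysis do not change. The small downside is that staff must follow the number where the tape's printed bands differ, for example a child at 112 mm who is orange in the 4-colour key. On a 3-colour tape the number is needed in any case, because the protocol's key gives red to both severe and moderate. The unit slip in the MUAC recording precision can be corrected to 1 mm in the same edit.

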***Dietary patterns***

The 24-hour recall will be analysed using the 11-food item to determine dietary diversity score. The FFQ will be analysed using SPSS version 23 for frequencies as daily, weekly, monthly, seasonal or never. Consumption of indigenous foods will be determined using frequencies. Food finder (MRC) will also be used to analyse the nutrient intakes.

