**2.5. Expected outcomes**

- Zinc and iron status of the intervention group will improve from baseline levels after consumption of the seeds for 6 months.
- Eating patterns of the participants will improve because of the nutrition education.
- Consumption of fruits and vegetables will increase because of the nutrition education.

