3.6.4.2.2. To measure the anthropometry of the study participants (Weight, Height, MUAC)

3.6.4.2.3. Determine the dietary diversity score of participants using 24- hour recall.

3.6.4.2.4. Determine dietary patterns of the study participants using FFQ.

3.6.4.2.5. To determine serum zinc concentrations among pre-school children using flame atomic absorption spectrophotometer before consuming *Cucurbita moschata* seeds.

3.6.4.2.6. To determine the iron status of pre-school children using hemoglobin, serum ferritin, transferrin receptor and C- reactive protein (CRP) before consuming the *Cucurbita moschata* (butternut) seeds.

**3.6.4.3. Design:** The study design will be post trial cross-sectional survey, similar to phase two. Quantitative data will be collected.

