**3.6.4.4. Measurements, procedures and analysis**

The following measurements will be done: demographic and environmental factors, anthropometrics, dietary intakes and patterns, and biochemical data. Same parameters and procedures, which were done at the baseline and described in section 3.6.2.4, will be followed. Data will be analysed using same procedures as described for baseline, with addition regression and ANOVA to measure changes from baseline to post intervention, and between experimental and control. See table 3.5 below. This is done to determine the changes in nutritional status that is likely to have occurred because of the intervention. A statistician will be consulted.

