**APPENDIX: D**

**SELECTED FOOD FREQUENCY QUESTIONNAIRE**

|  |  | **Average use** | | | | | | | |
| --- | --- | --- | --- | --- | --- | --- | --- | --- | --- |
| **Code** | **Food items** | **<1 month** | **1-3**  **Month** | **1 week** | **2-4**  **week** | **5-6**  **week** | **1 day** | **2-3**  **day** | **4+**  **day** |
| **Starchy food** | | | | | | | | | |
| **50** | Stiff MM porridge |  |  |  |  |  |  |  |  |
| **51** | Soft MM porridge |  |  |  |  |  |  |  |  |
| **52** | Fermented Soft MM porridge |  |  |  |  |  |  |  |  |
| **53** | Fermented Stiff MM porridge |  |  |  |  |  |  |  |  |
| **54** | Fermented home-made soft porridge |  |  |  |  |  |  |  |  |
| **55** | Samp |  |  |  |  |  |  |  |  |
|  | Rice |  |  |  |  |  |  |  |  |
|  | Macaroni |  |  |  |  |  |  |  |  |
|  | Spaghetti |  |  |  |  |  |  |  |  |
|  | Cooked maize cob |  |  |  |  |  |  |  |  |
|  | Roasted maize cob |  |  |  |  |  |  |  |  |
|  | Oats porridge |  |  |  |  |  |  |  |  |
|  | Muesli |  |  |  |  |  |  |  |  |
|  | Cornflakes |  |  |  |  |  |  |  |  |
|  | All bran |  |  |  |  |  |  |  |  |
|  | Brown Bread |  |  |  |  |  |  |  |  |
|  | Whole wheat bread |  |  |  |  |  |  |  |  |
|  | White bread |  |  |  |  |  |  |  |  |
|  | Home-made bread |  |  |  |  |  |  |  |  |
|  | Dumpling |  |  |  |  |  |  |  |  |
|  | Fat-cakes |  |  |  |  |  |  |  |  |
|  | Scones |  |  |  |  |  |  |  |  |
|  | Cakes |  |  |  |  |  |  |  |  |
|  | Muffins |  |  |  |  |  |  |  |  |
|  | Biscuits |  |  |  |  |  |  |  |  |
| **Protein foods (Meat and meat product)** | | | | | | | | | |
|  | Chicken drumstick (F/S) |  |  |  |  |  |  |  |  |
|  | Chicken thigh (F/S) |  |  |  |  |  |  |  |  |
|  | Chicken breast (F/S) |  |  |  |  |  |  |  |  |
|  | Chicken wing (F/S) |  |  |  |  |  |  |  |  |
|  | Stewed chicken feet |  |  |  |  |  |  |  |  |
|  | Chicken heads |  |  |  |  |  |  |  |  |
|  | Chicken liver |  |  |  |  |  |  |  |  |
|  | Chicken gizzard |  |  |  |  |  |  |  |  |
|  | Chicken necks |  |  |  |  |  |  |  |  |
|  | Chicken giblets |  |  |  |  |  |  |  |  |
|  | Stewed chicken |  |  |  |  |  |  |  |  |
|  | Barbequed/grilled chicken |  |  |  |  |  |  |  |  |
|  | Braai or dusty chicken |  |  |  |  |  |  |  |  |
|  | Stewed Turkey |  |  |  |  |  |  |  |  |
|  | Beef stew |  |  |  |  |  |  |  |  |
|  | Braai beef |  |  |  |  |  |  |  |  |
|  | minced meat |  |  |  |  |  |  |  |  |
|  | Ox Tripe |  |  |  |  |  |  |  |  |
|  | Ox Liver |  |  |  |  |  |  |  |  |

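### The FFQ records eight ordered frequency levels, but the stated analysis merges the three weekly and the three daily columns, so increases inside either band count as no change

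*Protocol*

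**What the plan says.** The form in Appendix D, headed "SELECTED FOOD FREQUENCY QUESTIONNAIRE", gives every food these eight ordered columns: "<1 month | 1-3 Month | 1 week | 2-4 week | 5-6 week | 1 day | 2-3 day | 4+ day".

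The Dietary patterns paragraph of the baseline data analysis section sets the coding: "The FFQ will be analysed using SPSS version 23 for frequencies as daily, weekly, monthly, seasonal or never". No section gives a recoding rule, a reason for the coarser labels, or a conversion to times per day or week. Two of the five labels, seasonal and never, have no column on the form.

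The FFQ is repeated after the intervention: "3.6.4.2.4. Determine dietary patterns of the study participants using FFQ". Section 3.6.4.4 reuses the baseline approach: "Data will be analysed using same procedures as described for baseline, with addition regression and ANOVA to measure changes from baseline to post intervention". The same sentence extends this to the comparison of experimental and control children.

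Section 2.5 lists among the expected outcomes: "Consumption of fruits and vegetables will increase because of the nutrition education". Another of the three is that eating patterns improve.

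**The concern.** The form separates levels that the analysis puts back together. Once, 2-4 times and 5-6 times a week all become weekly; once, 2-3 times and 4 or more times a day all become daily. An increase inside either band disappears before visits or arms are compared, so a real rise in consumption could be reported as no change.

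The other dietary instruments do not fill the gap. The 24-hour recall covers one day and is scored for dietary diversity, with food groups marked yes or no. The food diary covers food at home during the six intervention months and has no baseline. The FFQ is the only measure of habitual frequency taken both before and after.

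**Working it through.** **1. Mapping.** Following the column names:

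| Column on the form | Label in the analysis |
|---|---|
| <1/month | seasonal or never (assumed; no rule is given) |
| 1-3/month | monthly |
| 1/week, 2-4/week, 5-6/week | weekly |
| 1/day, 2-3/day, 4+/day | daily |

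Moves from 1/week to 5-6/week and from 1/day to 4+/day leave the label unchanged. The assumption about <1/month does not affect either example.

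**2. The Protocol's own figure.** There is no power statement for diet, only the total sample size in section 3.4. With N = 40291 and e = 0.05, n = 40291/(1 + 40291 × 0.05²) = 40291/101.7275 = 396.07. Adding 10% gives 396 × 1.10 = 435.6, so 436. The stated figure is reproduced; the printed line omits the square but its divisor uses it. An equal split gives 218 per arm.

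**3. Loss from merging.** For a proportional-odds shift, power ≈ Φ(ln OR × √(n(1 − Σp̄³)/6) − 1.96), where n is the number per arm and p̄ is the mean of the two arms' proportions at each level. The OR is set so that eight levels give 80% at n = 218: 1.60 for the uniform case and 1.61 for the others. The item distributions are assumptions, since the Protocol gives none.

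The relative efficiency of merging is the ratio of 1 − Σp³. Uniform case:
- eight levels: 1 − 8 × (1/8)³ = 0.984
- merged to 1/8, 1/8, 3/8, 3/8: 1 − (1 + 1 + 27 + 27)/512 = 0.891
- ratio: 0.891/0.984 = 0.905

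| Assumed use, % at levels 1 to 8 | Relative efficiency | Power, 8 levels | Power, merged labels |
|---|---|---|---|
| Uniform, 12.5 each | 0.905 | 80% | 75% |
| Mostly weekly: 5, 10, 20, 30, 15, 12, 6, 2 | 0.747 | 80% | 69% |
| Mostly daily: 3, 5, 7, 15, 15, 25, 20, 10 | 0.809 | 80% | 69% |
| Mostly rare: 35, 25, 15, 12, 6, 4, 2, 1 | 0.967 | 80% | 78% |

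The loss is about 2 to 11 points. If <1/month is instead counted as monthly, leaving three labels, merged power is 75%, 69%, 69% and 72%.

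**4. Shift wholly inside one band.** Start from the mostly-weekly case and move 15% of one arm from 1/week to 5-6/week: the first falls from 20% to 5% and the second rises from 15% to 30%. After merging, both arms have 65% in weekly and are identical. In 2,000 simulated trials with 218 per arm and a Mann-Whitney test, power was 75% on eight levels and 5-6% on the merged labels, which is the type I error rate.

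**5. Clustering.** Randomisation is by preschool, and the feeding-trial schematic gives 73 children per preschool. With an assumed ICC of 0.02 to 0.05, the design effect is 1 + 72 × 0.02 = 2.44 to 1 + 72 × 0.05 = 4.60. At the same OR, the eight-level 80% (1.96 + 0.84 = 2.80) becomes Φ(2.80/√2.44 − 1.96) = Φ(−0.17) = 43%, down to Φ(2.80/√4.60 − 1.96) = Φ(−0.65) = 26%. Merging then reduces an already low figure.

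**The case against.** The best defence is that the labels are a display choice. They are set out in the baseline survey section. Table 3.5 lists the FFQ only under descriptive statistics ("Frequency of inclusion of food item in the FFQ", reported as n and %), and scoring of a secondary questionnaire for an arm comparison is commonly left to a statistical analysis plan. Part of this stands: a frequency table by these labels is a reasonable description. But the Protocol does not leave the coding open. It states one, repeats the FFQ after the intervention and says the baseline procedures apply to the comparison. Nowhere does it keep the eight levels.

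Three stronger readings are tempting and lack support:

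- A reader might infer from Table 3.5 that merged FFQ labels will be compared between arms by an unordered test, at a further cost in power. The cell "Pearson’s Chi-square test/Fishers exact test" belongs to the row on micronutrient status by subject characteristics. The baseline analysis section names chi-square only among descriptive statistics, and section 3.6.4.4 names regression and ANOVA for change and arm comparison. No loss from an unordered test can be charged to the plan.
- A reader might infer that most of the expected change would fall inside a band. Nothing in the Protocol says so. Section 1.6 reports studies in which many children ate fruit or vegetables less than daily, so moves from weekly to daily, which the labels do capture, are plausible.
- A reader might infer that the trial's main result is affected. Section 2.3 makes zinc and iron status the primary aim. Diet appears as an expected outcome, and the 24-hour recall, nutrient intake analysis and food diary supply some further dietary information.

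**Conclusion.** The point holds as a minor one. The stated coding is coarser than the form, and it carries into the comparison of visits and arms for an outcome the Protocol expects to rise. That much follows from the text without any assumption.

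The size does not. The 2 to 11 point loss rests on assumed item distributions, an odds ratio chosen to give 80% on eight levels, 218 independent children per arm and an ordinal or rank analysis. For rarely eaten foods the loss is small. The within-band case is a constructed extreme showing what the coding cannot detect; it does not forecast the trial. Allowing for preschools lowers power under either coding.

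**What to change.** In the Dietary patterns paragraph, keep the present labels for the descriptive table only and say so. For comparisons between visits and arms, choose one of these in advance:

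- **Ordinal:** analyse all eight recorded levels as ordered categories.
- **Times per week:** give every level a fixed value and sum over the fruit items and over the vegetable items. Possible values are a fixed figure below 12/52 = 0.23 for <1/month; 2 × 12/52 = 0.46 for 1-3/month; 1; 3; 5.5; 7; 2.5 × 7 = 17.5 for 2-3/day; and 4 × 7 = 28 as the floor for 4+/day. List the rows that enter each sum, because the form has several overlapping rows for the same vegetable, such as spinach.

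In either case adjust for the baseline value and allow for preschool. State also how seasonal and never are obtained, since the form has no column for them.

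The cost is analysis wording; retaining the eight levels needs no new data. The small downside is that values for the levels, including the open-ended lowest and highest, must be fixed before the data are seen.
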